### **Rationale for PK Assessments**

In order to develop a PK structure model and evaluate the dependence of the PK of the active ceftobiprole on subject population covariates, collection of PK samples with rich sampling in a limited number of subjects and with sparse sampling in additional subjects are needed.

The combination of rich PK sampling and sparse PK sampling will be utilized to explore the effects of age, sex, weight, and renal function on plasma ceftobiprole concentrations.

## **4. STUDY POPULATION**

### **4.1. General Considerations**

Approximately 670 subjects will be randomized to achieve 532 clinically evaluable subjects, 266 subjects in each group.

The specific inclusion and exclusion criteria for enrolling subjects in this study are described in the following sections.

### **4.2. Inclusion Criteria**

Subjects must satisfy the following criteria to be enrolled in the study:

- Men or women, 18 years of age or older
- Women must be postmenopausal (for at least 1 year), surgically sterile (have had a hysterectomy or bilateral oophorectomy, tubal ligation, or otherwise be incapable of pregnancy), abstinent, or, if sexually active, be practicing an effective method of birth control (e.g., prescription oral contraceptives, contraceptive injections, intrauterine device, double-barrier method [e.g., condoms, diaphragm, or cervical cap with spermicidal foam, cream, or gel], contraceptive patch, male partner sterilization) before entry and continue to use the same method of contraception throughout the study
- Women must have a negative serum beta-human chorionic gonadotropin ( $\beta$ -hCG) or urine pregnancy test (depending on local regulations) before enrollment
- Willing to adhere to the prohibitions and restrictions specified in this protocol
- Subjects (or their legally acceptable representatives) must have signed an informed consent document indicating that they understand the purpose of and procedures required for the study and are willing to participate in the study

#### **Disease Specific**

Subjects with CAP severe enough to require hospitalization and treatment with i.v. antibiotics for at least 3 days (72 hours) defined as follows:

- Subjects must have a, b, c, d, AND e
  - a) Clinical diagnosis of acute bacterial pneumonia acquired in the community. Subjects must have resided in the community (i.e., NOT in a chronic care facility such as a nursing home or rehabilitation facility) and NOT have been hospitalized during the 14 days before the onset of

symptoms of pneumonia. Residence in an assisted-living facility where the subject has regular access to the community is allowed.

- b) Clinical signs or symptoms of acute bacterial pneumonia with AT LEAST 2 of the following criteria:
- Cough (new or increased over usual state)
  - Production of purulent sputum or a worsening in the character of sputum
  - Auscultatory findings on pulmonary examination of rales or evidence of pulmonary consolidation (dullness on percussion, bronchial breath sounds, or egophony)
  - Dyspnea or tachypnea (respiratory rate  $\geq 20$  breaths per minute), that is new or worse than usual state
  - New onset hypoxemia on room air ( $PO_2 < 60$  mmHg on arterial blood gas or  $O_2$  saturation  $< 90\%$  by pulse oximetry), or respiratory failure requiring mechanical ventilation.
- c) New radiographic infiltrates (not related to another disease process) consistent with the diagnosis of bacterial pneumonia
- d) Fever or leukocytosis/leukopenia (temporally associated with the onset of pneumonia symptoms) with AT LEAST 1 of the following:
- Fever (in the absence of antipyretics) defined as an axillary temperature  $> 37.5^\circ\text{C}$ , oral temperature  $> 38^\circ\text{C}$ , a tympanic temperature  $> 38.5^\circ\text{C}$ , a rectal temperature  $> 39^\circ\text{C}$ , OR hypothermia, defined as a rectal body temperature of  $< 35^\circ\text{C}$ .
  - Leukocytosis defined as an elevated total peripheral WBC count  $\geq 10 \times 10^9/\text{L}$  or  $\geq 15\%$  immature neutrophils (bands), regardless of total peripheral white count; OR leukopenia with total WBC  $\leq 4.5 \times 10^9/\text{L}$ .
- e) Severity of pneumonia requiring i.v. antibiotic therapy.

### 4.3. Exclusion Criteria\*

Potential subjects who meet any of the following criteria will be excluded from participating in the study:

---

\* This section of the protocol has been revised. Please refer to the section of this document entitled PROTOCOL AMENDMENTS (Amendment INT-3, 22 December 2006) for a detailed description of the specific changes.

## JNJ-30982081: Clinical Protocol 30982081-CAP-3001 - Amendment INT-3

- History of or suspected condition that may jeopardize adherence to protocol requirements (e.g., severe cardiac disease such that even minimal physical activity causes discomfort, New York Heart Association [NYHA] Class 4)
- History of or suspected hypersensitivity to any related anti-infective (including beta-lactam antibiotics such as penicillins and cephalosporins, oxazolidinones). Subjects in whom cephalosporins would be used as part of normal clinical practice are not excluded.
- History of or suspected condition or concurrent treatment that would be contraindicated by the prescribing information for ceftriaxone or linezolid
- History of or suspected severe renal impairment, (i.e.,  $Cl_{Cr} \leq 30$  mL/min or oliguria  $<20$  mL/h unresponsive to fluid challenge) or any form of dialysis
- History of or suspected hepatic dysfunction (total bilirubin, or alanine aminotransferase [ALT], or aspartate aminotransferase [AST]  $\geq 3$  times the upper limit of the normal range [ULN]).
- History of suspected extra-pulmonary infection, including concomitant meningitis, endocarditis, septic arthritis, or osteomyelitis
- Known to be human immunodeficiency virus (HIV) positive with CD4 counts of  $\leq 0.2 \times 10^9/L$  ( $\leq 200$  cells/mm^3). (Subjects with HIV and  $>0.2 \times 10^9/L$  [ $>200$  cells/mm^3] may be included)
- Presence of neutropenia, (absolute neutrophil count [ANC]  $\leq 0.5 \times 10^9/L$  [ $<500$  Neutrophils [polymorphonuclear leukocytes] [PMNs/mm^3]) severe anemia (hemoglobin  $<6.5$  g/dL), or severe thrombocytopenia ( $<49.9 \times 10^9/cm$ ). *Note: Subjects receiving immunosuppressive therapy who are expected to reach a nadir of  $<500$  PMNs/mm^3 during administration of study drug should not be enrolled*
- Previous enrollment in this study or any other ceftobiprole protocol
- Have received an experimental drug or used an experimental medical device within 30 days before the planned start of treatment
- Is pregnant or breast-feeding
- Employees of the investigator or study center, with direct involvement in the proposed study or other studies under the direction of that investigator or study center, as well as family members of the employees or the investigator

**Clinical conditions that may interfere with assessments of efficacy:**

- Sustained shock
- Subjects with any of the following pulmonary conditions:
  - known bronchial obstruction or a history of postobstructive pneumonia

- primary lung cancer or another malignancy to the lungs unless surgically resected
- cystic fibrosis
- lung abscess
- pleural effusion as a primary source of infection
- active tuberculosis
- suspected or known pneumonia due to aspiration, atypical bacteria (*Legionella* spp, *Mycoplasma pneumoniae*, and *Chlamydia pneumoniae*), viruses, or *Pneumocystis jiroveci* (*carinii*).

Note – Subjects with asthma or chronic obstructive pulmonary disease are not excluded provided they meet the criteria of acute new-onset pneumonia.

#### **Microbiological conditions that may interfere with assessments of efficacy:**

- Systemic antimicrobial therapy for more than 24 hours in the 3 days before enrollment.

Exception: Systemic antimicrobial therapy for more than 24 hours is permitted in the case of a subject with an infection caused by microbiologically confirmed pathogen(s) that are resistant to the previous antimicrobial agents (e.g., pneumonia due to a macrolide resistant staphylococci or pneumococci being treated with a macrolide).

## **4.4. Prohibitions and Restrictions**

Potential subjects must be willing to adhere to the following prohibitions and restrictions during the course of the study to be eligible for participation.

- Women must avoid pregnancy through the use of contraception or abstinence during the course of this study. The same method of contraception must be continued throughout the study. Pregnancy testing will be done at screening and at the TOC visit.
- Use of nonstudy antibacterial agents is prohibited until after the LFU.

## **5. RANDOMIZATION AND BLINDING**

### **5.1. Overview**

Randomization will be used to avoid bias in the assignment of subjects to treatment, to increase the likelihood that known and unknown subject attributes (e.g., demographics and baseline characteristics) are evenly balanced across treatment groups, and to enhance the validity of statistical comparisons across treatment groups. Blinded treatment will be used to

reduce potential bias during data collection and evaluation of clinical endpoints.

## 5.2. Procedures

Subjects will be assigned to 1 of 2 treatment groups based on a computer-generated randomization schedule prepared by the sponsor before the study. The randomization will be balanced between the 2 treatment groups by using randomly permuted blocks. Subjects will be stratified at entry by PSI score to 1 of 2 strata:  $\leq 90$  and  $\geq 91$ . Subjects will also be stratified by the need for anti-staphylococcal therapy (placebo or linezolid) based on signs, symptoms, and medical history at enrollment. Based on this randomization code, the study drug will be packaged and labeled for each subject. Medication code numbers will be preprinted on the study drug labels and assigned as subjects qualify for the study and are randomly assigned to treatment. An unblinded monitor will perform drug accountability.

Central randomization will be implemented in conducting this study. The subject number and treatment regimen will be assigned after phoning into the Interactive Voice Response System (IVRS) provided by a vendor designated by the sponsor. The caller must use their own user ID and PIN, and then give the requested subject details (e.g., subject initials and subject's date of birth). Based on this information, the IVRS will assign a unique subject number and treatment regimen, which will dictate the treatment assignment for that subject.

The investigator will not be provided with randomization codes. The codes will be maintained within the IVRS, which has the functionality to allow the investigator to break the blind for an individual subject.

Under normal circumstances, the blind should not be broken until all subjects have completed the study and the database is finalized. Otherwise, the blind should be broken only if specific emergency treatment would be dictated by knowing the treatment status of the subject. In such cases, the investigator must contact the sponsor. If the investigator is unable to contact the sponsor, the investigator may in an emergency determine the identity of the treatment by telephoning IVRS. The sponsor must be informed as soon as possible. The date, time, and reason for the unblinding must be documented in the appropriate section of the case report form (CRF) and in

the source document. The fax copy received from the IVRS indicating the code break must be retained with the CRF.

## 6. DOSAGE AND ADMINISTRATION

### 6.1.1. Overview\*

The unblinded pharmacist will be responsible for preparation of the study drug for each subject in such a way that investigators and staff remain blinded to the study drug being administered. Colored sleeves will cover infusion bags and line tubings as needed to maintain the blind. The study drug regimen is discussed in Section 6.1.2, Intravenous and Oral Switch Study Drug Regimen and Section 6.1.3, Linezolid/Placebo Therapy for ceftriaxone-resistant *S. pneumoniae* and *S. aureus*.

All subjects should receive the first dose of study drug as quickly as possible after randomization. In order to ensure subject safety and to avoid potential overdose, if a subject has received a nonstudy antibiotic before enrollment, the timing of the first dose of study drug may be delayed so it is consistent with the recommended dosing interval of the nonstudy antibiotic. In the event that a subject received a nonstudy, beta-lactam antibiotic (e.g., penicillin, cephalosporin, carbapenem) before enrolling in the study, the timing of the first dose of study cephalosporin (ceftobiprole or ceftriaxone) may be delayed. All subjects should receive a minimum of 3 days (72 hours [9 doses of ceftobiprole or 3 doses of ceftriaxone; with placebo administered as described below to maintain the blind]) of the i.v. study drug and should continue on i.v. therapy while hospitalized. At the discretion of the investigator, subjects may receive study drug infusions as outpatients or through a home-care agency, provided they meet all other protocol requirements, but all i.v. study drug infusions must be administered and monitored by a qualified nurse, a qualified member of the study staff, or an infusion specialist. If after 3 days (72 hours) the subject's signs and symptoms have improved from baseline as defined in the protocol and the subject will be discharged from the hospital, the i.v. therapy may be discontinued at the investigator's discretion and the subject treated with oral cefuroxime axetil 500 mg every 12 hours.

---

\* This section of the protocol has been revised. Please refer to the section of this document entitled PROTOCOL AMENDMENTS (Amendment INT-3, 22 December 2006) for a detailed description of the specific changes.

Subjects should continue i.v. study drugs for as long as they are hospitalized. However, as discussed above, it is recognized that some subjects will improve to the point where it is appropriate, based on local medical practice, to be discharged from the hospital and to complete antimicrobial therapy with oral medication. To align with this practice, it will be possible for subjects to complete antimicrobial therapy by switching to oral medications (cefuroxime axetil as discussed above) provided ALL of the criteria in Section 9.1.4, Criteria for Intravenous to Oral Switch, are met. Additionally, if it is the local custom for subjects to remain hospitalized for extended periods beyond the need for i.v. therapy for social or logistical reasons, the subject may, in this case, be switched to oral therapy if deemed necessary, while still hospitalized.

#### **6.1.2. Intravenous and Oral Switch Study Drug Regimen**

Study drug (i.v. plus oral) will be administered for 5 to 10 days. The total duration of study drug therapy (i.v. plus oral) for all subjects will be a minimum of 5 days and a target of 7 days. If, in the investigator's opinion, a subject requires additional days of study therapy, the duration of the therapy may be extended (up to a maximum of 10 days). Therapy can be extended to a maximum of 14 days after approval by the sponsor's Medical Monitor, for subjects with a history of persistent bacteremia or X-ray evidence of necrotizing pneumonia.

At the investigator's discretion, therapy may be stopped when the infection is considered clinically cured (based on normalization of the clinical signs and symptoms of infection and improvement in the chest X-ray, and after a minimum of 5 total treatment days).

Ceftobiprole and ceftriaxone will be administered as follows:

- Ceftobiprole will be administered at a dose of 500 mg in 250 mL of 5% dextrose in water (D5W) every 8 hours at a constant-rate i.v. infusion over a period of 120 minutes (must not be administered through an i.v. line containing sodium chloride [e.g., saline, Ringer's Lactate solution]). Further details of the preparation and administration of ceftobiprole are presented in Attachment 2, Preparation and Administration of Intravenous Infusion Solutions of Ceftobiprole Medocaril (500 mg dose).
- Ceftriaxone will be administered at a dose of 2 g in 50 mL of D5W every 24 hours by i.v. infusion over a period of 30 minutes.

Placebo will be used to maintain the blind for both cephalosporins:

- For subjects randomized to ceftobiprole, a 30-minute i.v. infusion of placebo of 50 mL of D5W will be given every 24 hours concomitantly with ceftobiprole and will begin with the first dose of ceftobiprole.
- For subjects randomized to ceftriaxone, a 120-minute i.v. infusion of placebo of 250 mL of D5W will be given every 8 hours concomitantly with ceftriaxone, and will begin with the first dose of ceftriaxone.

Note: The 30-minute infusion should be administered first (placebo or ceftriaxone), followed by the 120-minute infusion (ceftobiprole or placebo), to ensure that active treatment is delivered to the subject as soon as possible.

Optional oral switch regimen:

- Cefuroxime axetil 500 mg every 12 hours orally.

### **6.1.3. Linezolid/Placebo Therapy for Ceftriaxone-resistant *S. Pneumoniae* and *S. Aureus*\***

#### **Antibiotic coverage of Ceftriaxone-resistant *S. pneumoniae* (CRSP)**

Linezolid or placebo should be added to study treatment for subjects with confirmed CRSP provided the sensitivity of the isolate to linezolid has been confirmed.

#### **Anti-staphylococcal Therapy**

If the incidence of MRSA in CAP isolates is prevalent (i.e., greater than 15%) in the local institution or region, or additional subject-specific risk factors are present, such as a history of prior MRSA infection or a surveillance culture positive for MRSA, linezolid/placebo should be added to cover the possibility of *S. aureus* based on the presence of:

- Gram-stain from adequate sputum with gram-positive cocci in clusters as predominant organism (>10/hpf) or respiratory culture positive for *Staphylococcus* within 72 hours before randomization.

In addition, 2 or more of the following criteria:

- Temperature >39°C

---

\* This section of the protocol has been revised. Please refer to the section of this document entitled PROTOCOL AMENDMENTS (Amendment INT-3, 22 December 2006) for a detailed description of the specific changes.

- Heart rate >140 beats per minute
- Respiratory rate >30 breaths per minute
- Hemoptysis
- Leukopenia
- Influenza symptoms within last 2 weeks (cough, coryza, fever)
- Necrotizing lesion(s) on chest X-ray or CT scan
- Known local case(s) of PVLpositive *S. aureus* infections

Linezolid/placebo will be discontinued at 48 hours if *S. aureus* is not isolated from the baseline cultures.

If the subject meets the criteria listed above but a Gram stain cannot be immediately obtained (i.e., the sputum sample is obtained at night), linezolid can be added empirically until the Gram stain results are available. If the results do not show gram-positive cocci in clusters from an adequate specimen, then treatment with linezolid should be discontinued.

If the incidence of MRSA in CAP isolates is not prevalent (i.e., less than 15%) in the local institution or region, the investigator may wait for definitive confirmation of MRSA sensitive to linezolid in the respiratory specimen collected within 72 hours before randomization prior to adding linezolid/placebo.

The following dosage of linezolid/placebo will be administered:

- Linezolid will be administered to those subjects randomized to ceftriaxone, at a dose of 600 mg in 300 mL of D5W every 12 hours by i.v. infusion over a period of 60 minutes. Placebo of 300 mL of normal saline (NaCl 0.9% solution) will be administered to those subjects randomized to ceftobiprole, at a volume of 300 mL every 12 hours by i.v. infusion over a period of 60 minutes. Normal saline (NaCl 0.9% solution) will replace D5W as the placebo solution for ceftobiprole in order to minimize the amount of free water delivered to subjects who are randomized to receive additional coverage with linezolid/placebo as follows:

| Ceftobiprole Arm                                               | Ceftriaxone Arm                                              |
|----------------------------------------------------------------|--------------------------------------------------------------|
| Placebo (50 mL D 5 W) every 24 hours                | Ceftriaxone (2g in 50 mL D 5 W) every 24 hours    |
| Ceftobiprole (500 mg in 250 mL D 5 W) every 8 hours | Placebo (250 mL normal saline ) every 8 hours)        |
| Placebo (300 mL normal saline ) every 12 hours          | Linezolid (600 mg in 300 mL D 5 W) every 12 hours |

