Target duration of study drug treatment (i.v. and oral) for all subjects will be a minimum of 5 days and a target of 7 days. If, in the investigator's opinion, a subject requires additional days of study therapy, the duration of the therapy may be extended (up to a maximum of 10 days). Subjects will be evaluated at Day 5 and 10 while on therapy.

Linezolid or placebo will be added as concomitant therapy based on initial signs and symptoms suggestive of MRSA or *S. aureus*. Linezolid or placebo should be discontinued once infection with MRSA or CRSP is ruled out.

Therapy can be further extended to a maximum of 14 days after approval by the sponsor's Medical Monitor. Subjects will be evaluated at Day 14 while on prolonged therapy.

Late Follow-up Visit is by telephone contact. Subjects reporting signs or symptoms consistent with pulmonary infection should be evaluated by a physician.

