## 15. ETHICAL ASPECTS

### 15.1. Study-Specific Design Considerations

There are 5 aspects of this study design requiring ethical justification.

Surveillance studies of susceptibility patterns of microorganisms known to cause CAP suggest that both study regimens (ceftobiprole/placebo or ceftriaxone/linezolid) should be highly efficacious in treating such infections. The comparator regimen consists of approved antibiotics. Ceftriaxone is commonly recommended to treat CAP. Linezolid is included initially to provide treatment for resistant pathogens (e.g., PRSP, MRSA) that are included in the spectrum of activity of ceftobiprole. Once these resistant pathogens are ruled out as the cause for CAP, the linezolid will be discontinued in order to decrease exposure of subjects to unnecessary antibiotics. However neither treatment regimen is active against *Legionella* spp, which are uncommon causes of CAP but have the potential to cause severe, even fatal disease. An overwhelming number of cases of CAP due to *Legionella* spp are caused by *L. pneumophila*. The protocol excludes subjects with CAP known or suspected to be caused by *Legionella* spp and mandates a urine test for legionella antigen that is highly specific and sensitive.

The second issue is the selected dose of ceftobiprole. The PK modeling data of ceftobiprole suggest that the current dosing regimen should be highly efficacious in treating CAP due to *S. pneumoniae* (including penicillin and ceftriaxone-resistant strains), *S. aureus* (including MRSA and VRSA), *H. influenzae*, and the majority of strains of enteric gram-negative rods (e.g., *K. pneumoniae*).

The third issue is that there are no efficacy data in the use of ceftobiprole for treatment of pulmonary infections or infections due to *S. pneumoniae*. The only data in subjects is from the Phase 2 studies in complicated skin infections and used a different dose of ceftobiprole. However, in vitro and animal studies of ceftobiprole demonstrate that it behaves in a similar fashion to other cephalosporins. Cephalosporins have been used as first line therapy for CAP for over 2 decades and it is anticipated that ceftobiprole will be equally efficacious. Additionally, an IDMC will assess the efficacy data in an ongoing fashion. The same IDMC will also review efficacy data from the 2 ongoing Phase 3 studies in nosocomial pneumonia.

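### The protocol gives inconsistent conditions for stopping linezolid/placebo, and they conflict for a subject started empirically whose baseline culture grows ceftriaxone-resistant pneumococcus but no S. aureus

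*Protocol*

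**What the plan says.** Four sets of current statements govern when linezolid/placebo starts or stops.

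- **Section 6.1.3, Anti-staphylococcal Therapy, and the matching Synopsis text.** The start rule covers the species, not only resistant strains: "linezolid/placebo should be added to cover the possibility of *S. aureus* based on the presence of" a Gram stain or culture finding plus at least two further criteria. The stop rule is "Linezolid/placebo will be discontinued at 48 hours if *S. aureus* is not isolated from the baseline cultures". It makes no exception for CRSP and does not mention methicillin susceptibility.
- **Section 3.1, notes to the study diagram, start.** "Linezolid or placebo will be added as concomitant therapy based on initial signs and symptoms suggestive of MRSA or *S. aureus".
- **Section 3.1, notes to the study diagram, stop.** "Linezolid or placebo should be discontinued once infection with MRSA or CRSP is ruled out". No time limit is given.
- **Section 15.1.** The add-on is explained as cover for resistant organisms, with penicillin-resistant pneumococcus (PRSP) and MRSA as examples. Then: "Once these resistant pathogens are ruled out as the cause for CAP, the linezolid will be discontinued". Again there is no time limit.
- **Section 6.1.3, CRSP subsection, and the matching Synopsis text.** "Linezolid or placebo should be added to study treatment for subjects with confirmed CRSP provided the sensitivity of the isolate to linezolid has been confirmed". This subsection has no stopping condition of its own.

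The table in Section 6.1.3 shows that subjects randomized to ceftobiprole receive saline in this slot and subjects randomized to ceftriaxone receive linezolid.

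**The concern.** The three stopping statements depend on different organisms: S. aureus as a species, MRSA or CRSP, and an open list of resistant pathogens. Only the first has a time limit. Two sites with the same culture report could each follow the protocol and still treat the subject differently.

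The consequence falls on one arm. Stopping the slot removes an active drug only from ceftriaxone subjects, because ceftobiprole subjects lose only saline. If the 48-hour sentence is applied to a subject with CRSP, ceftriaxone continues without the agent that another part of Section 6.1.3 adds for that organism. That is first a subject-protection matter. Statistically, it is a possible source of unplanned variation in how the comparator is delivered, among subjects who have a baseline pathogen and so enter the mITT population and the by-pathogen summaries.

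**Working it through.** The protocol gives no figure on this point, so the main check sets the passages side by side. The table takes a subject started empirically for suspected S. aureus and applies each statement to each possible baseline result. The diagram note is read as requiring both organisms to be ruled out.

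| Baseline result | 48-hour sentence (6.1.3, Synopsis) | Diagram note (3.1) | Section 15.1 | CRSP subsection (6.1.3, Synopsis) |
|---|---|---|---|---|
| MRSA | no stop | no stop | no stop | does not apply |
| Methicillin-susceptible S. aureus | no stop stated | stop | stop | does not apply |
| CRSP, no S. aureus | stop at 48 hours | no stop | CRSP not named, list is open | add, if linezolid-sensitive |
| None of these | stop at 48 hours | stop, no time given | stop, no time given | does not apply |

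**CRSP without S. aureus.** The first column says stop. The second gives no stop, because CRSP has not been ruled out. The fourth calls for the therapy. Read literally, these cannot all be followed. If the diagram note is instead read as satisfied once either organism is ruled out, it would permit stopping, but the 48-hour sentence would still oppose the CRSP subsection.

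**Methicillin-susceptible S. aureus.** The 48-hour sentence is not triggered, because S. aureus was isolated, but it does not order continuation. The diagram note and Section 15.1 stop the therapy once their named organisms are ruled out. A site could comply with all of them by stopping, so the text is unclear rather than contradictory.

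**No relevant organism.** The direction agrees and only the timing differs.

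**Scale, on assumptions only.** The protocol gives neither the share of subjects with CRSP nor the share of those who would meet the anti-staphylococcal start criteria.

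- Comparator subjects: 670 / 2 = 335.
- CRSP in 1 to 3% (assumption): 0.01 × 335 ≈ 3 to 0.03 × 335 ≈ 10 subjects.
- Of these, 10 to 25% also started empirically (assumption): 0.10 × 3.35 ≈ 0.3 to 0.25 × 10.05 ≈ 2.5 subjects.
- If every one of them would otherwise be cured and instead fails: 0.3 / 335 ≈ 0.1 to 2.5 / 335 ≈ 0.75 percentage points, against a 10-point margin.

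The last step is deliberately extreme, so under these assumed shares the range is an upper bound. It is not an estimate.

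**The case against.** The best defense is structural. Section 6.1.3 has two headed parts. The 48-hour sentence sits under the anti-staphylococcal heading and CRSP has its own heading, so one can say that the first ends empirical staphylococcal cover and the second takes over once CRSP is confirmed. The amendment log fits this, since it records that the pneumococcal condition was removed from the 48-hour sentence for clarity. In addition, Section 9.3.2 asks that the investigator be told of suspected resistant pathogens as early as possible, including at the 48-hour report, and Section 9.1.3 requires daily assessment in hospital.

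Much of this stands. A site that reads both subsections together would probably not leave a confirmed CRSP subject without the add-on, and early reporting lowers the risk further. It does not remove the conflict. The diagram note applies the CRSP condition to therapy begun for suspected MRSA or S. aureus, which is the group the 48-hour sentence governs. Even on the two-heading reading, therapy would stop at 48 hours and restart if CRSP were confirmed later, whereas the diagram note would keep it running in between. Being told of the organism does not tell the investigator which instruction applies.

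A reader might also infer that the passages contradict each other for methicillin-susceptible S. aureus and that this weakens the comparator. The documents do not support that. The 48-hour sentence never orders continuation, and Section 1.1.2 describes ceftriaxone as active against S. aureus other than MRSA.

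**Conclusion.** The stopping conditions are inconsistent in current text and should be reconciled. The conflict is real for a narrow group: subjects started under the anti-staphylococcal criteria whose baseline culture grows CRSP and no S. aureus. For methicillin-susceptible S. aureus the text is unclear.

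Two stronger readings should be resisted. One is that the comparator as a whole is undefined. It is not: ceftriaxone with or without linezolid is the stated comparator, the doses are specified, and only the duration of the add-on in a small subset is in doubt. The other is that the conflict consumes a material part of the noninferiority margin. Counting every assumed CRSP subject as a failure would give 3 / 335 = 0.9 to 10 / 335 = 3.0 points, but that includes subjects who never met the empirical start criteria, to whom the 48-hour sentence does not apply.

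The effect on the overall cure-rate difference cannot be quantified from the protocol and is probably small. The reason to act is subject protection and consistent delivery of the comparator. It is not a demonstrated bias in the primary analysis.

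**What to change.** Reconcile both parts of Section 6.1.3, the two matching Synopsis paragraphs, the notes to the study diagram in Section 3.1, and Section 15.1 into one rule, worded identically wherever it appears. The rule should state the action for each baseline result: MRSA, methicillin-susceptible S. aureus, CRSP, and none of these. It should also say:

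- whether a time limit applies, and what happens while culture or susceptibility results are pending;
- whether both named organisms or only one must be ruled out;
- how the anti-staphylococcal and CRSP subsections relate, by explicit cross-reference.

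Clinical experts must decide which action applies in each case. This review takes no position on that.

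The cost is amended protocol wording and a note to sites. Sample size, randomization and the planned analysis are unaffected. Section 7 already requires each intravenous administration to be recorded, so the duration of linezolid/placebo by baseline pathogen can be tabulated without new data collection to show whether practice differed.
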